#### Computed Tomography

All study subjects will undergo inspiratory 64-channel CT scans of the chest with the following standard parameters: 0.8 mm reconstructed slice thickness, 0.4 mm slice interval, matrix size 512 x 512, range -500 to 1500, 120 kV, 40 mAs.

A trained professional research assistant will evaluate the scan for technical completeness, compliance with protocol, adequacy of inspiration, and presence of motion artifact. The stability of CT measurements for CT scanner used in the study will be monitored by monthly scanning using a custom phantom designed for this study.

While conducting this cross-sectional study, we identified an optimal quantitative CT assessment protocol by using Airway Inspector based on the Slicer computer program (Harvard University) for lung densitometry [23]. In addition to qualitative assessment of 3D lung reconstruction, Slicer software allows for quantitative measurements of lung tissue density based on Hounsfield units. Such a tool provides the opportunity for automated measurement and quantitative comparisons between study groups based on an objective emphysema scoring system.

#### Electrocardiography

A standard 12-lead ECG taken by Fukuda Denshi FX-8222 Cardimax will be performed for each study subject by employing strictly standardized procedures. Research staff will be trained to properly place electrodes. At least four cardiac cycles will be taken from each of 12 leads. The machine runs at 50 mm/sec. The following ECG parameters will be evaluated by a trained clinical researcher: waves and complexes, presence and description of ECG abnormalities including pathologic q-waves, ST elevation, ST depression, T-wave inversion, hypertrophy, QRS axis deviation, block, and arrhythmia. ECGs will be visually inspected for technical errors and interpreted by a qualified cardiologist. The prevalence of specific ECG abnormalities as well as grouped abnormalities will be reported for each study group. We will measure and analyze associations between COPD and ECG abnormalities, crude and adjusted by sex, age, and smoking status.

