## Introduction

Chronic obstructive pulmonary disease (COPD), the fourth leading cause of death in Kazakhstan, is a global public health problem. It is the third leading cause of death globally, accounting for 3.2 million deaths worldwide in 2015 [1]. In Kazakhstan, an expected 1.4 million people may have COPD based on estimations from neighboring countries [2]. COPD negatively affects the quality of life and is a major health care burden [3]. It is the third leading cause of hospital readmission within 30 days [4]. Cigarette smoke is the most common risk factor for COPD [5]. COPD is traditionally defined by airflow obstruction and includes emphysema, gas trapping, and chronic bronchitis [6]. Systemic effects (eg, on heart and muscles) and associated comorbidities (eg, heart failure, metabolic disorders, sleep apnea syndrome, and depression) may complicate the course of disease, posing challenges in the management of COPD [7-9].

Recently, we conducted a cross-sectional study of COPD among men and women aged 40-59 who currently smoke cigarettes, do not smoke, and stopped smoking 1-5 years ago [10]. We demonstrated that based on the COPD Assessment Test (CAT), respiratory symptoms are common in current smokers who have spirometric values that are generally considered to be within the normal range. We identified a relatively low percentage of participants with obstructed respiratory functions on spirometry. It was higher among current smokers (5.5%) compared to former and nonsmokers (3% among both groups). We found that 42% of current smokers had COPD symptoms based on a CAT score of ≥10—a prevalence of symptoms that was far greater than that among former smokers and controls who never smoked (17% and 12.5%, respectively). In addition, smoking cessation significantly reduced functional exercise incapacity, that is, inability to walk 450 meters within 6 minutes in the 6-Minute Walk Test (6MWT; 11% among ex-smokers compared to 16.7 % among current smokers).

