## Methods

### Study Design

The goal of this study is to evaluate whether the presence of respiratory symptoms, functional exercise incapacity, and COPD exacerbation rate across time are the same between the exposure group (users of iQOS with HeatSticks) and the control group (smokers of combustible cigarettes) through hypothesis testing.

In addition to this confirmatory goal, we would like to explore trends in spirometry results, chest CT scan results, prevalence of impaired quality of life, metabolic syndrome, abnormalities found by electrocardiography (ECG), physical exams, and serum lab tests among those who use iQOS with HeatSticks and those who currently smoke combustible cigarettes.

Exacerbation history will be collected prospectively (every 3 months) with the use of the adapted version of our proprietary SymptoMaster (Web, iOS, and Android) [16], and Medintel (Web) apps [17]. Symptoms history will be analyzed by clinical investigators. Should there be symptoms identified that are relevant to COPD, clinical investigators will approach health care organizations (serving participants in primary health care catchment area) to obtain ambulatory records of the use of antibiotics and/or systemic glucocorticoids or a health care utilization event.

Our primary confirmatory outcome variables are (1) presence of respiratory symptoms defined by CAT≥10, (2) functional exercise incapacity, and (3) exacerbation rate. The main exposure variable is smoking status (users of combustible cigarettes and users of iQOS with HeatSticks). The study groups are defined as:

Individuals (men and women) aged 40-59 years (inclusive) with a minimum of 10 pack-year smoking history who switched to and predominantly use the heated tobacco product iQOS with HeatSticks (exposure group). Predominant use of iQOS with HeatSticks is defined as >70% use.Individuals (men and women) aged 40-59 years (inclusive) who are currently smoking combustible cigarettes with a minimum of 10 pack-year smoking history (control group)

Pack-years will be calculated by taking the average number of cigarettes smoked per day divided by 20 and multiplied by the number of years smoked.

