### Inclusion and Exclusion Criteria

The study’s inclusion criteria comprise the following: male or female, aged 40-59 years, smoking history ≥10 pack-years (for all groups), and ability to follow study procedures. The exclusion criteria consist of the following:

pregnant womenlegally incapable individualspatients with history of chronic infectious and noninfectious lung disease except asthma (eg, pulmonary fibrosis, bronchiectasis, cystic fibrosis, tuberculosis) diagnosed prior to or during the first visit to the KAPM COPD Centerprevious surgical excision of at least one lung lobe (or having undergone a lung volume reduction procedure)active cancer of any localization under treatmentsuspected cancer of any localizationmetallic objects in the chestrecent eye surgery (within 6 months prior to the visit)episode(s) of myocardial infarction within 6 months prior to the visit or another form of acute or chronic coronary heart disease, history of heart rhythm abnormality with episode of arrhythmia within 6 months prior to the visit or long lasting that requires continuous drug therapyacute episode of cerebrovascular ischemic attack within 12 months prior to the visitchest or abdominal surgery performed within 6 months prior to the visitcontraindications to salbutamol or refusal to inhale salbutamolchest radiation therapy within 12 months prior to the visitradiology diagnostic procedures of chest within 6 months prior to the visitrecent (6 weeks before visit) respiratory tract infection (colds, flus), fever of any etiology with increasing temperature >37^°^C at the time of the visit and 2 weeks prior to the visitsignificant history of alcohol abuse or consumption of more than recommended units of alcohol per week (28 units male and 21 units female)positive screening test for HIV antibodies or positive screening for TB, if available at the time of first visitelevated blood pressure (systolic) ≥160 mmHg at the time of visitemployees of Philip Morris International and first-degree relatives who are employees of Philip Morris International

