### Study Procedures

#### Recruitment

We will select 800 current smokers and 400 users of iQOS with HeatStick based on the inclusion criteria. The recruitment strategy for smokers of combustible cigarettes and participants who use iQOS with HeatStick includes word-of-mouth communication to friends and spouses of individuals who participated in the cross-sectional study, advertisements, social media engagement (ie, Facebook, Instagram, WhatsApp chats), and outreach to community groups. In addition, we will recruit users of iQOS with HeatSticks at iQOS stores in Almaty, Kazakhstan.

To achieve comparability of comparison groups at baseline, the matched-pair cohort study design will be implemented, where a pair contains one iQOS with HeatSticks user and two conventional cigarette users. The following variables will be utilized for matching: gender, age (±3 years), education (as a proxy for socioeconomic status), and number of pack-year (±5 pack-years) as the baseline exposure level (number of pack-year).

Once potential participants who meet inclusion criteria are identified, they will undergo further medical assessment at the KAPM COPD Center to test for exclusion criteria and to start baseline comprehensive assessment.

The study will include (1) baseline comprehensive assessment at outset of the study during the enrollment period, which is expected to last for about 6 months (4^th^quarter of 2017 to 1^st^-3^rd^quarters of 2018); (2) annual comprehensive assessments at 2^nd^-4^th^quarters of 2018-2022; (3) periodic prospective case finding and exacerbation history assessment on quarterly basis (every 3 months), semiannual, and annual basis; and (4) continuous COPD case-finding activities based on patient self-assessment and professional clinical assessment during periodic visits to KAPM dedicated primary care unit.

**Table 1 table1:** Sample size calculations.

Primary confirmatory variable	Estimated value of outcome variable in exposure group	Estimated value of outcome variable in control group	Sample size exposed/ nonexposed	Adjusting sample size for anticipated dropouts
Symptomatic smokers defined by CAT ≥10	17%	42.8%	23/46	31/62
6MWT <450 m	11%	16.7%	260/520	347/694
Annual exacerbation rate	0.05	0.1	255/510	340/680

Baseline comprehensive assessment at outset of the study (4^th^quarter of 2017) and annual assessments (4^th^quarters of 2018-2020) will include the following:

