### Computer-Assisted Personal Interviewing

KAPM has developed an electronic data capture system in the form of its proprietary computer-assisted personal interviewing app. The app is available for tablet personal computers and will be modified to be implemented in the cohort study to collect, store, and transmit data related to a personal survey interview. The questionnaire will be designed to collect data on possible COPD risk factors including history of smoking, current smoking, level of smoking exposure (in pack-year), passive smoking, occupational and environmental hazards, including dusts, chemicals, and indoor fuel pollution. The questionnaire will contain covariates: age, gender, ethnicity, education, occupation, and self-reported morbidity. It will also include questions to address COPD exacerbations and to record the use of combustible cigarettes, iQOS with HeatSticks, electronic cigarettes, and other alternatives, as well as iQOS switch date.

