We will apply a three‐stage reporting framework [27]. Model 1 will report the crude analysis (without any adjustments for confounders), Model 2 will report the semi‐adjusted analysis (including the following a priori defined covariates of gender, age, number of pack-year at base-line), and Model 3 will present the fully adjusted model (including all the covariates as in Model 2 plus those covariates that have discrepancies across two cohorts and change the estimate of association). The matching variables can be ignored in the model if we have exactly two controls for each participant in the iQOS cohort. Because of dropouts and other reasons, that will be impossible to achieve. There will be some confounder effect remaining, which means we have to include matching variables in the analysis. Model diagnostic plots will be generated to test model assumptions, for example, normality of deviance residuals.

We will also use two methods of propensity score analysis (PSA)—stratification on the propensity score and inverse probability weighting using the propensity score [28]—to adjust for confounders that may vary in study groups.

For missing data analysis, we will use missing at random assumptions. Missing values will be handled by multiple multivariate imputation in R. We will analyze five copies of the data, each with missing values imputed, in the GEE/GLMM multivariate analysis. The estimates of association will then be averaged according to Rubin’s rule [29] to produce a single mean estimate and adjusted standard errors.

To address dual usage, switching, and quitting, we will use several methods. First, we will implement the intention-to-treatment strategy, that is, we will adjust only for baseline confounders and evaluate the exposure effect as if all study participants remain under the exposures at the baseline until end of follow‐up. Second, we will evaluate the exposure effect censoring switchers and quitters from the analysis. Third, particularly for dual usage, we will model two exposures, iQOS and conventional cigarette usage, as weighted sums of doses calculated in pack-years. Weights will depend on the importance of the different periods, where the closest period will have the highest weight.

Analysis will be done using R [19]. The Bonferroni correction of the significance level will be applied to account for three confirmatory hypotheses being tested in the study, so an alpha <.017 (0.05/3) will be considered significant.

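### The exploratory COPD-ECG association is adjusted for product group but not for pack-years, so cumulative smoking can inflate the adjusted estimate; a minor point that costs one covariate to mend

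*Protocol article*

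**What the plan says.** The Electrocardiography section gives this analysis its own covariate list: "We will measure and analyze associations between COPD and ECG abnormalities, crude and adjusted by sex, age, and smoking status".

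Study Design says what smoking status means: "The main exposure variable is smoking status (users of combustible cigarettes and users of iQOS with HeatSticks". It is a two-level variable.

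Cumulative dose is a separate variable throughout the article:
- It is an entry criterion with a floor and no ceiling: "smoking history ≥10 pack-years (for all groups".
- It is a matching variable between the two product cohorts: "number of pack-year (±5 pack-years) as the baseline exposure level".
- It is a separate questionnaire item (Computer-Assisted Personal Interviewing): "history of smoking, current smoking, level of smoking exposure (in pack-year), passive smoking".
- It is a fixed covariate of Model 2 in the statistical analysis section: "including the following a priori defined covariates of gender, age, number of pack-year at base-line".

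On the link between smoking and COPD, the Introduction says: "Cigarette smoke is the most common risk factor for COPD".

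**The concern.** By adjusting for smoking status, the plan accepts that smoking can confound the COPD-ECG association. The form of smoking it adjusts for carries no dose. Heavier lifetime smokers are more likely to have COPD and plausibly also more likely to have ECG abnormalities, so some or all of an adjusted association could reflect pack-years.

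What is at stake is interpretation. A reader told that the estimate is adjusted for smoking status may assume that smoking has been dealt with. The article says its secondary endpoints are there to generate hypotheses, and this one could send follow-up work in the wrong direction.

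**Working it through.** The article gives no figure for this association, so there is none to reproduce. The check has three steps.

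**1. Does anything else in the plan control dose in this model?**
- *Product group.* Matching within 5 pack-years makes the two cohorts similar in dose, so the group term says almost nothing about pack-years. Matching does nothing to balance dose between participants with and without COPD.
- *Age.* Study Design computes pack-years as cigarettes per day / 20 × years smoked. Age can stand in for part of the years, but not for intensity. Two people of the same age who each smoked for 30 years have 10/20 × 30 = 15 pack-years at 10 a day and 40/20 × 30 = 60 at 40 a day.
- *Models 1 to 3.* They are set out for the effect of tobacco product on outcomes. Nothing extends them to a model in which COPD is the explanatory factor.

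Dose is therefore uncontrolled in the model as stated.

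**2. What dose effect on COPD is plausible from the article's own figures?** The Introduction reports obstruction in 5.5% of current smokers and 3% of both former smokers and nonsmokers ("It was higher among current smokers (5.5%) compared to former and nonsmokers").
- Crude odds ratio: (0.055/0.945) / (0.03/0.97) = 0.0582/0.0309 = 1.88.
- Assuming a mean of 25 pack-years (not in the documents) and a log-linear effect: 1.88^(1/2.5) = 1.29 per 10 pack-years, about 1.3.

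**3. What bias follows?** Data were simulated with no COPD effect on ECG abnormality and with pack-years raising both. ECG abnormality was then regressed on COPD, sex, age and product group, with and without pack-years.

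- From the article: 1200 participants (400 and 800), COPD 5.5%, that is 0.055 × 1200 = 66 cases, and a floor of 10 pack-years.
- Assumed: ECG abnormality 20%, the pack-year spread, the dose effects, and the correlation of pack-years with age.

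Results with a COPD odds ratio of 1.3 per 10 pack-years:

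| Setting | ECG odds ratio per 10 pack-years | Odds ratio as planned | Rejection at 5% |
|---|---|---|---|
| n = 1200, age correlation 0.2 to 0.4 | 1.1 | 1.00 to 1.12 | 5% to 7% |
| same | 1.2 | 1.06 to 1.19 | 5% to 9% |
| same | 1.3 | 1.10 to 1.30 | 5% to 16% |
| n = 1200, pack-year SD 10, 300 datasets | 1.3 | 1.09 | 7% |
| n = 1200, pack-year SD 15, 300 datasets | 1.3 | 1.28 | 17% |

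In the last two settings, adding pack-years brought the odds ratio to 1.00 in both, with rejection of 5% and 6%.

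Very large samples (400,000 each, age correlation 0.2), with odds ratios of 1.3 for COPD and 1.2 for ECG, show the dependence on spread. At a pack-year SD of about 7, 12 and 16, the model as planned gave 1.03, 1.08 and 1.21. With pack-years added it gave 0.99, 0.98 and 1.01. With weaker effects (1.2 for COPD, 1.1 for ECG), the model as planned gave 1.01, 1.01 and 1.05 at the same spreads.

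With 300 datasets, the Monte Carlo standard error at a true 5% is √(0.05 × 0.95/300) = 1.3 percentage points. Rejection of 6% or 7% is therefore not clearly different from nominal.

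**The case against.** **The analysis is peripheral.** It is one sentence in a measurement section, outside the three confirmatory outcomes. That stands, and it sets the weight of the point.

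**The article promises associations, not causal effects.** An association that pack-years explain is still an association. This is fair, and rejection rates under no effect do presuppose the question of whether COPD matters beyond smoking. But an adjusted estimate is offered precisely to remove other explanations, and here the main one is left in.

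**The ECG side is wholly assumed.** The article gives neither a prevalence of ECG abnormality nor any dose effect on it. Its exclusion criteria remove coronary heart disease, recent or drug-treated arrhythmia and systolic pressure of 160 mmHg or more, which may weaken the smoking-ECG link. This stands, and is why the result is a range that starts at no bias.

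**A condensed article may leave fuller covariate sets to an analysis plan.** For an unstated list that would settle the matter. Here a list is stated, and it differs from the article's own Model 2 on exactly this variable.

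**A reader might infer a large bias.** With an odds ratio of 1.5 per 10 pack-years for both conditions, simulated spurious odds ratios reach about 1.8. The article's figures do not support that input. At 25 pack-years it implies 1.5^2.5 = 2.76 for the average smoker against none, compared with the crude 1.88. Former smokers, who also have cumulative exposure, show the same 3% as nonsmokers, although their pack-years are not given.

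**Conclusion.** The point holds as a minor one. As stated, the adjusted COPD-ECG model leaves cumulative smoking uncontrolled, and if dose raises both conditions the estimate is biased upward, away from the null when there is no true association. Under the assumptions above, the spurious odds ratio is about 1.0 to 1.3 and rejection at the 5% level about 5% to 17%. With weak dose effects or a narrow pack-year spread it is negligible. The lower part of that range cannot be told from nominal error, and the documents do not say where in it the study will fall.

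The result rests on three things outside the documents: the pack-year distribution, the dose effect on ECG abnormality, and the 20% prevalence. The COPD dose effect is only loosely supported, by a crude contrast and an assumed mean.

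A reader might also infer that the main product comparison is compromised. It is not: pack-years are matched on and included in Model 2 there, and the confirmatory outcomes, the Bonferroni level and the sample size do not depend on this analysis.

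**What to change.** In the Electrocardiography section, change the description of the analysis to: *crude and adjusted for sex, age, product group and baseline pack-years (continuous)*. Naming product group in place of smoking status also removes any doubt about what that term covers, and the added covariate brings the sentence into line with Model 2.

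The cost is one more term in an exploratory model. The variable is already collected, so no new data, visits or design change are needed.

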#### Physical Exam

Clinical investigators were trained to conduct the pulmonary (ie, percussion and inspection) exam and technique for listening to second heart sounds. Two Stanford Medicine 25 modules [20,21] will be used as study materials in hands-on sessions. The prevalence of individual pathological findings will be presented for each study group.

#### Anthropometry

Anthropometric measurements will include height, weight, waist circumference, heart rate, blood pressure, and pulse oximetry.

#### Six-Minute Walk Test

The 6MWT is a simple and effective test that measures the distance that a patient can quickly walk on a flat, hard surface in a period of 6 minutes. A 100-ft hallway is needed, and no exercise equipment or advanced training for technicians is required [24].

#### Laboratory Data

Blood donated by the study participants will be processed at the KAPM COPD Center for shipment, analysis, and intermittent (at -20°C) and long-term (deep freeze at -80°C) storage at HealthCity Laboratory in accordance with biobanking standards. The HealthCity Laboratory will perform the following assays: CBC, blood cholesterol level, HDL, LDL, triglycerides; glucose, hemoglobin A1C; C-reactive protein; and fibrinogen.

In addition, blood will be stored in order to perform testing for sRAGE, ICAM1, CCL20, and other potential biomarkers at a later stage. Biomarker testing will be done using enzyme-linked immunosorbent assay (ELISA) and/or aptamers analysis. Testing for other biomarkers, such as CDH1, CDH13, SERPINA7, Interleukin 16 (plasma level), and genotyping will also be considered depending on availability of the tests and their value in COPD diagnosis. We are also exploring technical capabilities for “-omics” studies, additional biomarkers, and tobacco-specific nitrosamines assay in urine.

Previously reported findings, particularly when combined with other studies of individual biomarkers, suggest a panel of blood biomarkers including sRAGE (advanced glycosylation end-product receptor), the biomarker of increased emphysema percentage in the lungs independent of gender, age, airflow limitation, body mass index, and current smoking status. Decreased ICAM1 levels correlate with increased severity of emphysema on CT scans, independent of smoking status, FEV1, and other covariates CCL20 (macrophage inhibitory protein 3a), inversely and significantly associated with emphysema. Interleukin 16 (IL-16; a multifunctional cytokine that has been associated with autoimmune and allergic diseases) is positively associated with age and body mass index and negatively associated with current smoking and emphysema in the upper lobes. An integrated “-omics” analysis in a very large cohort identified an association between decreased IL-16 and emphysema and discovered a novel IL-16 local expression quantitative trait loci (cis-eQTL) [25]. Thus, IL-16 plasma levels and IL-16 genotyping may be useful in a personalized medicine approach for lung disease.

